#### End Line Qualitative Assessment

In the postintervention phase, qualitative assessments (FGDs and IDIs) are done to ascertain the feasibility of intervention uptake and understand facilitators and barriers in implementation rollout. Key stakeholders for FGDs include those randomly selected LHSs and LHWs who took part in the delivery of the intervention. Moreover, for IDIs, CPs in the postintervention qualitative phase also include those individuals who receive the digital counseling intervention, namely, the SPs. All participants provided written informed consent prior to their interviews.

### Sample Size Calculations

For the baseline screening survey, the sample size is calculated using OpenEpi (version 3.01; Emory University) [38]. Assuming a 30% prevalence of depression and anxiety symptoms among adults, at a 5% level of significance and 80% power, 323 people are required to assess point prevalence of depression and anxiety [39]. Catering to 10% refusals, the final sample size is 366 individuals.

For the change in mental health literacy of CHWs, a total of 72 LHSs and LHWs are required to detect a mean difference of 1.5 (SD 3.9) in pre- and posttraining knowledge and skills scores, assuming 5% significance level and 80% study power [40].

For receiving mPareshan app-based intervention, the sample size for recruitment of SPs is calculated using Medcalculator (version 19.8; MedCalc Software). Assuming a mean difference between pre- and postintervention of PHQ-9 scores of 1.5 (SD 5.6; mean score at baseline=11.61 and postintervention=10.1), the minimum sample size required at a 5% level of significance and 80% power is 112. Considering a 10% attrition rate, with some oversampling, the expected sample size is 123 for recruiting participants for the mPareshan intervention and demonstrating a reduction in symptoms [41].

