### Data Analysis

Baseline and end line data collected from respondents is being exported from REDCap to SPSS (version 21; IBM Corp). Frequency and proportion will be used to report categorical variables. Depending on the distribution of anxiety or depression scores of SPs and knowledge or skills scores of health workers, paired *t* tests or McNemar’s chi-square tests will be used to evaluate the change in outcomes. The mean difference with 95% CIs will be reported. A *P* value of <.05 will be considered statistically significant.

All interviews will be transcribed in English. Using NVivo (Lumivero), content analysis will be conducted on all IDI and FGD transcripts, and codes will be organized into either emergent or predetermined categories by the researchers. Commonalities and differences across the data will be identified and clustered around thematic sections. Verbatim quotes will be added to complement the themes. RE-AIM framework will be used to describe the feasibility outcomes [33].

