## Results

Data were collected in 2022-2023. At the time of this submission (April 2024), we are analyzing the results of 366 individuals who participated in the baseline prevalence survey, the change in knowledge and skills of 72 health workers who took the mPareshan training, change in anxiety and depression scores of 98 SPs recruited for app-based counseling intervention, and stakeholder perceptions gathered from 8 FGDs and 18 IDIs as part of qualitative assessments. Final data cleaning and data analysis are ongoing and the results will be disseminated through peer-reviewed publications in 2024.

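### The sample size of 72 health workers does not follow from its printed inputs: 80% power needs 56, and 72 gives about 90%, so an input is wrong or was left out

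*Protocol article*

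**What the plan says.** The third stated aim (Aims and Objectives) is to observe the effect of the adapted mhGAP training on the knowledge and skills of LHWs and LHSs. For this aim, Sample Size Calculations states that "a total of 72 LHSs and LHWs are required to detect a mean difference of 1.5 (SD 3.9"). The outcome is the workers' score before and after the training, and the calculation is made "assuming 5% significance level and 80% study power".

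No refusal or attrition allowance, correlation, multiplicity adjustment, software or sidedness is given for this calculation. The other two calculations in the section do print allowances: 10% for refusals in the household survey and 10% for attrition among screen positives.

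Data Analysis says that, depending on the distribution of the scores, "paired *t* tests or McNemar’s chi-square tests will be used to evaluate the change in outcomes", and that "A *P* value of <.05 will be considered statistically significant". Results reports that the data under analysis include "the change in knowledge and skills of 72 health workers who took the mPareshan training".

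**The concern.** The sentence prints a size, a difference, an SD, a significance level and a power. Given the design, any four of these determine the fifth, so the sentence can be checked without outside information, and it does not close.

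If only the power was misprinted, nothing of substance changes. If the difference or the SD was misprinted, the change that the training comparison can detect at 80% power is not the one the article tells readers. The consequence is for how the planning statement is read, not for the validity of the test that will be run.

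**Working it through.** **Inputs.** Difference 1.5, SD 3.9, 5% significance, 80% power and n = 72 come from Sample Size Calculations. The paired t test comes from Data Analysis. Two assumptions are mine: the test is two-sided, and 3.9 is the SD of the within-person differences.

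**Check of the method on the neighbouring figure.** For screen positives, the section gives a difference of 1.5, SD 5.6, 5% and 80%, and says that "the minimum sample size required at a 5% level of significance and 80% power is 112". A two-sided paired t test (noncentral t distribution) gives exactly 112. The normal formula gives (2.8016 × 5.6 / 1.5)² = 109.4, rounded up to 110.

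**Health workers, normal formula.** n = ((z₀.₉₇₅ + z_power) × SD / difference)².
- 80% power: (2.8016 × 3.9 / 1.5)² = 53.06, rounded up to 54.
- 90% power: (3.2415 × 3.9 / 1.5)² = 71.03, rounded up to 72.

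**Health workers, paired t test.** The power is that of a t test on n − 1 degrees of freedom with noncentrality (1.5 / 3.9) × √n.

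| n | Power |
|---|---|
| 55 | 79.99% |
| 56 | 80.7% |
| 72 | 89.6% |
| 73 | 90.0% |

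So 80% power needs 56 and 90% needs 73. The printed 72 exceeds 56 by 16, or 16/56 = 29%. By the normal approximation, power at 72 is 90.4%.

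**Variants that do not give 72 (80% power throughout).**

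| Variant | n |
|---|---|
| One-sided test | 44 |
| Bonferroni for two scores (alpha 0.025) | 67 |
| Efficiency loss for a Wilcoxon test (0.955 or 0.864) | 59 or 65 |
| Inputs at their rounding limits (1.45 to 1.55; 3.85 to 3.95) | 51 to 61 |
| 10% dropout added to 56 | 63 |
| Two independent groups | 107 per group |

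**Changes that do give 72, or come within one of it.**
- 90% power: 72 by the normal formula, 73 by the t test.
- A difference of about 1.31 with SD 3.9 at 80% power: 72. (A difference of 1.30 gives 73.)
- An SD of differences of about 4.48 with difference 1.5 at 80% power: 72. (An SD of 4.50 gives 73.)
- A non-completion allowance of about 22%: 56 / 0.78 = 71.8, so 72.
- 3.9 as the SD at each time point with pre-post correlation 0.34: SD of differences = 3.9 × √(2 × 0.66) = 4.48, giving 72. (A correlation of 0.33 gives 74 and 0.35 gives 71.)

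None of these is printed for this calculation, and the first three replace a figure that is.

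**The case against.** The strongest reply is that nothing printed need be wrong, because an input may only have been left out. The article does not say whether 3.9 is the SD of the change or of the score at one time point, and a condensed article may omit a correlation or an allowance that the full protocol states. This stands, and it is why the conclusion is worded as wrong or left out. It is weakened, but not removed, by two facts: the other two calculations in the section print their allowances, and the article calls 72 the number required.

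The second reply is that the discrepancy is harmless. Most of this stands too. On the printed inputs 72 is more than enough, 72 trained workers are being analysed, the data were collected in 2022-2023, and neither the planned tests nor the confidence intervals use the planning power.

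Three stronger readings are tempting, and the document supports none of them:
- A reader might infer that 72 was computed at 90% power and misreported as 80%. This is plausible, but it gives 72 only by the normal formula. The t method that reproduces 112 gives 73.
- A reader might infer from the exact match at 112 that the method cannot explain the mismatch. The match shows how 112 can be obtained. The article names software for the survey and the screen-positive calculations but not for this one, so it does not show how 72 was obtained.
- A reader might infer that the training comparison is undermined. On the printed inputs it has more power than claimed.

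**Conclusion.** The point holds as an internal inconsistency. With 3.9 as the SD of the paired differences and a two-sided 5% paired t test, the stated inputs require 56 health workers, not 72, and 72 gives 89.6% power, not 80%. The size, the power or another input is wrong, or an input was not printed; the article does not allow a choice between these. If the printed difference and SD are right, the error is in the safe direction and the comparison is more than adequately powered. If one of them is not, the detectable change at 80% power differs from the one stated, for example about 1.31 rather than 1.5 with the SD kept at 3.9. This is a reporting correction of modest consequence, with no bearing on recruitment or on the planned tests.

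**What to change.** Go back to the original calculation and rewrite the sentence in one of two ways.
- If the difference and SD are as printed and no allowance was used: say that 72 health workers give about 90% power to detect a 1.5-point difference (SD of differences 3.9), and that 56 would give 80%.
- If 80% power was intended: keep it and print what actually leads to 72. That could be a difference of about 1.31, an SD of differences of about 4.48, a statement that 3.9 is a single-time-point SD together with the correlation used (about 0.34), or 56 plus a stated non-completion allowance of about 22%. The value printed should come from the original calculation, not be chosen to fit 72.

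In either case, say whether the SD is that of the differences. The cost is one sentence. The number of health workers, the data and the analysis are unaffected.

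### The article reports 98 screen positives recruited, below its own minimum of 112 for 80% power, and does not restate the power (about 75%, or 70% after 10% attrition)

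*Protocol article*

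**What the plan says.** All planning figures are in the Protocol article, Methods, Sample Size Calculations.

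- **Intervention sample.** The inputs are "Assuming a mean difference between pre- and postintervention of PHQ-9 scores of 1.5", with "SD 5.6; mean score at baseline=11.61 and postintervention=10.1". From these, "the minimum sample size required at a 5% level of significance and 80% power is 112".
- **Attrition.** "Considering a 10% attrition rate, with some oversampling, the expected sample size is 123".
- **Screening survey.** This is sized separately, to estimate prevalence. "Assuming a 30% prevalence of depression and anxiety symptoms among adults", the section finds that "323 people are required to assess point prevalence of depression and anxiety", and raises this to 366 for 10% refusals.

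Under Study Procedure Outline and HH Survey, survey respondents with mild or moderate symptoms become the SPs who are invited to counselling. The Results section (and the Abstract) reports 366 survey participants and an analysis of the "change in anxiety and depression scores of 98 SPs recruited for app-based counseling intervention". The Discussion refers to the small number enrolled, but only in relation to generalizability. The Data Analysis section plans paired tests, a mean difference with 95% CI, and significance at P<.05.

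**The concern.** The article gives a minimum for 80% power and reports a recruited number below it, and nothing connects the two. End Line Quantitative Assessment treats the change in scores as the indicator of effectiveness, and Data Analysis judges it at P<.05. A reader who takes the power from the sample size paragraph would therefore read a non-significant PHQ-9 result as coming from a test with a 20% chance of missing a true 1.5-point change. With the number recruited, that chance is 25% to 30%.

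The planned numbers also do not fit together. The attrition allowance falls slightly short, and the survey was not sized to supply 123 SPs.

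**Working it through.** **Inputs** (Sample Size Calculations unless noted): mean change δ = 1.5; SD 5.6, taken as the SD of the paired change; 5% significance; 80% power; attrition 10%; recruitment figure 123; assumed prevalence 30%; survey size 366. From Results: 366 surveyed, 98 SPs recruited. Sidedness is not stated. Two-sided is assumed because it reproduces 112; a one-sided test gives about 87.

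**1. Reproduce the plan's figure.**
- Normal approximation: n = [5.6 × (1.960 + 0.842) / 1.5]² = 109.4, so 110.
- Exact paired t test (noncentral t with n − 1 degrees of freedom and noncentrality (1.5/5.6)√n): the smallest n with power of at least 80% is **112**, with power 80.2%.

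The stated 112 is therefore right for its inputs.

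**2. Power with the number recruited** (same exact t model, δ = 1.5, SD 5.6).
- 98 is 112 − 98 = 14 below the minimum and 123 − 98 = 25 (25/123 = 20%) below the recruitment figure.
- If 10% of the 98 are lost, 98 × 0.90 = 88.2, so 88 remain.

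| Analysed | Noncentrality (1.5/5.6)√n | Power | Difference detectable at 80% power |
|---|---|---|---|
| 112 | 2.83 | 80.2% | 1.50 |
| 98 | 2.65 | 74.7% | 1.60 |
| 88 | 2.51 | 70.0% | 1.69 |

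The normal approximation gives nearly the same: 75.5% and 71.0% power, and detectable differences of 1.58 and 1.67.

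**3. Attrition allowance.**
- 112 × 1.10 = 123.2, which matches the stated 123.
- 123 × 0.90 = 110.7, so about 111 remain, just under 112 (power at 111 is 79.9%).
- Full cover for 10% loss is 112 / 0.90 = 124.4, so 125.

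The 123 therefore contains no oversampling beyond the attrition allowance, and that allowance is itself two short.

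**4. Expected supply from the survey.**
- Taking 30% as the eligible share: 366 × 0.30 = 109.8, so about 110, before exclusions and non-consent.
- Share of 366 needed: 112/366 = 30.6% for the minimum and 123/366 = 33.6% for the recruitment figure.
- Number to screen in order to expect 123 at 30%: 123/0.30 = 410.
- Observed: 98/366 = 26.8%.

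If exactly 30% of 366 independent respondents were expected to be positive, 112 or more would occur with probability about 42%, and 123 or more with probability about 7%.

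**The case against.** The strongest reply is that a sample size section records the plan. The 112 is correct, the shortfall arose in conduct, and 98 is openly reported. No sentence claims that 98 gives 80% power. All of this stands: the sample size formula contains no error, and a reader who infers a false power claim for the 98 goes further than the text. What remains is that the article has both numbers and does not say that one is below the other.

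Three further objections limit the point.

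- **The 70% figure is conditional.** The article does not say whether 98 counts all SPs enrolled or only those with both assessments. If all 98 have end line scores, power is about 75% and the loss is about 5 points.
- **The survey did not make 80% power unattainable.** A reader might infer that it could supply at most 110 SPs, or only 97 (30% of 323). The documents support neither. The number surveyed was 366, and 110 is an expected value, not a ceiling. With 110 analysed, power is 79.5%, essentially the target. The 30% is also ambiguous: eligibility is anxiety or depression, so a per-condition prevalence of 30% could give a larger pool. Exclusion of people on treatment or with severe symptoms and danger signs, and non-consent, act the other way.
- **Much of the remedy is already planned.** The 95% CI is specified, and the article describes a feasibility trial and a pilot. This lowers the stakes but does not reconcile the figures.

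**Conclusion.** The concern holds as a reporting inconsistency of moderate size. The article's own minimum of 112 was not reached, and the power statement was left as it stood. For the planned 1.5-point change, power is about 75% with 98 analysed and about 70% with 88, a loss of roughly 5 to 10 percentage points. The detectable difference at 80% power is 1.6 to 1.7 points.

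These figures assume a two-sided paired t test and that 5.6 is the SD of the change; both are supported by the reproduction of 112. The lower power figure also assumes that the 10% attrition has still to be taken from the 98.

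The attrition allowance (123 against 125) and the expected survey yield (about 110 against 123) are secondary. The first has almost no effect on power. The second shows that the two sample sizes were not linked, and it rests on 30% being the eligible share.

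**What to change.** Rewrite the intervention part of Sample Size Calculations, or add a statement beside the recruited number in Results, to say:

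- 98 SPs were recruited against 123 planned, with 125 needed to cover 10% attrition in full; remove the reference to oversampling.
- State whether 98 is the number enrolled or the number with both assessments.
- Power for a 1.5-point PHQ-9 change (SD 5.6) is about 75% with 98 analysed, or about 70% if 10% are lost; the difference detectable at 80% power is 1.6 to 1.7 points.
- The survey of 366 had an expected yield of about 110 positives at 30%, before exclusions and non-consent, and was not sized to supply 123; say whether the 30% refers to either condition or to each.

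Base the conclusion on the planned mean difference and 95% CI, and do not present the comparison as powered at 80%. In the Discussion, name reduced power alongside generalizability as a consequence of the small sample.

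The cost is one paragraph and a less favourable power figure. No participants are added and no analysis changes. The article reports that analysis was still under way, so the correction could accompany the results.

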### Data Analysis

Baseline and end line data collected from respondents is being exported from REDCap to SPSS (version 21; IBM Corp). Frequency and proportion will be used to report categorical variables. Depending on the distribution of anxiety or depression scores of SPs and knowledge or skills scores of health workers, paired *t* tests or McNemar’s chi-square tests will be used to evaluate the change in outcomes. The mean difference with 95% CIs will be reported. A *P* value of <.05 will be considered statistically significant.

All interviews will be transcribed in English. Using NVivo (Lumivero), content analysis will be conducted on all IDI and FGD transcripts, and codes will be organized into either emergent or predetermined categories by the researchers. Commonalities and differences across the data will be identified and clustered around thematic sections. Verbatim quotes will be added to complement the themes. RE-AIM framework will be used to describe the feasibility outcomes [33].

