#### Baseline Quantitative Assessments

##### HH Survey

A baseline survey was conducted in 5 Talukas of Badin District, Sindh to identify individuals having symptoms of anxiety and depression. Trained field staff visit HH for data collection. Data collectors are provided training on administering the GAD-7, PHQ-9, and entering data electronically using REDCap (Research Electronic Data Capture; Vanderbilt University) on a tablet. Data are also collected on basic sociodemographic variables.

The GAD-7 scale is used to screen symptoms of anxiety disorders. This scale has 7 items, and each item is rated on a sliding scale of 0-3 based on the frequency of occurrence of the symptoms. The maximum possible score is 21 and the minimum score is 0. Scores of 5, 10, and 15 are taken as the cutoff points for mild, moderate, and severe anxiety, respectively. GAD-7 has 89% sensitivity and 82% specificity for detecting generalized anxiety disorder at a cutoff score of 10 [35].

The PHQ-9 screens for symptoms of depression. There are 9 items rated on a scale of 0 to 3. The maximum possible score is 27 and the minimum score is 0. Scores 5, 10, 15, and 20 represent cutoff points for mild, moderate, moderately severe, and severe depression, respectively. PHQ-9 has 88% sensitivity and 88% specificity for detecting major depression at a cutoff score of 10 [36].

Participants with mild or moderate symptoms of anxiety and depression on the GAD-7 and PHQ-9 are identified as SPs and invited to take part in the mPareshan app–based counseling sessions.

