### Phase 3: Postintervention

#### End Line Quantitative Assessment

After the conclusion of the sixth mental health counseling session, an end line HH survey is conducted by trained data collectors using the same PHQ-9 and GAD-7 psychometric tools. This determines the change in mean symptomatic scores of anxiety and depression among intervention recipients (SPs), indicating intervention effectiveness (clinical outcome).

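### The choice between a paired t test and McNemar's test depends on the distribution of the scores; the paired t test rests on the within-person differences, and a switch would put the P value on a different estimand

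*Protocol article*

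**What the plan says.** The Data Analysis section makes the choice of test conditional: "Depending on the distribution of anxiety or depression scores of SPs and knowledge or skills scores of health workers". One candidate is the paired t test. For the other, the wording is "McNemar’s chi-square tests will be used to evaluate the change in outcomes". The section does not mention the paired differences. It then adds, with no condition attached, "The mean difference with 95% CIs will be reported".

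The outcome itself is a mean change. End Line Quantitative Assessment says of the second survey: "This determines the change in mean symptomatic scores of anxiety and depression among intervention recipients (SPs". Sample Size Calculations sizes the SP part on a pre-post difference in "PHQ-9 scores of 1.5 (SD 5.6; mean score at baseline=11.61 and postintervention=10.1", and concludes that "the minimum sample size required at a 5% level of significance and 80% power is 112".

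Eligibility is worded in two ways. The HH Survey section reads: "Participants with mild or moderate symptoms of anxiety and depression on the GAD-7 and PHQ-9 are identified as SPs". The section on eligibility for the intervention instead admits people who are mild or moderate on either condition. By the cutoffs in HH Survey, mild to moderate is 5-14 on both scales.

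**The concern.** A paired t test is a one-sample test on the differences. The shape of the baseline or end line scores is not one of its assumptions, yet that shape is what the rule examines. SPs are also selected on the very baseline scores that would be examined, so the rule may respond to the eligibility band and not to any problem with the analysis of change.

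At stake is agreement between the P value and the planned outcome. McNemar's test compares paired proportions. If it replaces the paired t test, the article would report a mean difference with its CI beside a P value for a change in the proportion above some cut, and the Data Analysis section defines no cut. The study was sized for the mean difference, and 98 SPs were recruited against a stated minimum of 112, so there is little power to give away.

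**Working it through.** **1. The plan's own figure.** Inputs from Sample Size Calculations: difference 1.5, SD 5.6, 5% significance (taken as two-sided), 80% power.

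- Normal approximation: n = (SD × (1.960 + 0.842) / difference)² = (5.6 × 2.802 / 1.5)² = 109.4, rounded up to 110.
- Noncentral t for paired differences: 111.3, rounded up to 112.

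So 112 reproduces with 5.6 read as the SD of the paired differences. The planned analysis therefore already rests on the differences. Paired t power is 80.2% at 112 and 74.7% at the 98 SPs given in Results.

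**2. What a check of the scores would react to.** The plan names no normality test, so Shapiro-Wilk at 5% is an assumption, as are the score shapes. Rejection rates at 98 SPs (98-112 in the row for uniform or skewed scores):

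| Eligibility reading | Assumed shape | Baseline scores rejected | Differences rejected |
|---|---|---|---|
| Both scales 5-14 (HH Survey) | normal underlying | 100% | 9-44% |
| Both scales 5-14 | uniform or right-skewed | about 100% | 23-69% |
| Either scale, no score of 15 or more | normal underlying | 54-100% | 9-20% |
| Either scale, no upper cap | normal underlying | 15-68% | – |
| Either scale (with or without a cap on severe scores) | right-skewed, correlated | about 99% | 37-53% |

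In the last row about 20% of SPs have a PHQ-9 score below 5 and 4-5% above 14, so the restriction is only partial there.

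**3. Whether the paired t analysis is sound anyway.** Coverage of the 95% interval was 94-96% across the eligibility readings. Type I error was 4.8-5.2% with skewed scores confined to 5-14, and 5.9-6.0% with strongly skewed (exponential) differences, at 98 and 112.

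**4. What a switch costs.** Assume bivariate normal scores with means 11.61 and 10.11, SD of differences 5.6, score SD s of 4.0 or 5.6, and a cut at 10. The implied correlation is 1 − 5.6²/(2s²), which is 0.02 for s = 4.0 and 0.50 for s = 5.6.

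- s = 4.0: proportion at or above 10 is 0.656 before and 0.511 after. Discordant cells are 0.318 and 0.173, so the difference d = 0.145 and the sum D = 0.491.
- s = 5.6: 0.613 before and 0.508 after. Discordant cells are 0.222 and 0.117, so d = 0.105 and D = 0.339.

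Approximate McNemar power = Φ[(d√n − 1.96√D) / √(D − d²)]. At n = 98 this gives 54% and 43%. Simulation of the test gives 54% and 44% at 98, and 60% and 49% at 112. Simulated power at 112 is 30-33% for a cut at 5 and 41-45% for a cut at 15. The paired t test on the same simulated data has about 74-75% at 98 and 80-81% at 112.

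**The case against.** The strongest objection is that the planned outcome survives. A reader might infer from the rule that the mean change can be dropped altogether. The text does not support that: the mean difference and its CI are promised unconditionally, so only the test and its P value can switch. This stands and limits the harm.

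A reader might also infer that every SP score is cut off at 5 and 14. That holds for both scales only under the HH Survey wording. Under the either-condition wording one scale may lie outside the band, and baseline rejection can fall to 15-68%. This also stands. The restriction says nothing about the health workers' knowledge and skills scores; for them only the general point about differences applies.

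The plan does not say which scores are examined or how, and its phrase may be shorthand that includes change scores. That is possible, and an article need not spell out a diagnostic. But the text that is there names the scores as the basis for choosing the test, and that basis is wrong as written.

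The differences can themselves be non-normal (9-69% rejection above), so a switch would not always be groundless. Non-normal differences did little harm to the paired t analysis at these sizes, however.

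Finally, most of the power loss comes from McNemar's test being the alternative. In a simulation with normal differences (mean 1.5, SD 5.6, n = 98), power was 76% for the paired t test and 74% for the signed-rank test. This is fair: the score-based rule does material damage because of the test it leads to, so the repair must deal with both.

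**Conclusion.** The point holds in a limited form. The rule examines the wrong quantity, and for SPs that quantity is shaped wholly or partly by eligibility. If it fires, the P value moves from the planned mean change to a dichotomised outcome, while the estimate and CI remain on the mean change. At 98 SPs, power would fall from about 75% to about 44-54%, with little gain in validity.

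The power figures assume normal scores, a cut at 10 and an SD of differences of 5.6; the rejection rates assume Shapiro-Wilk and particular score shapes. How often the rule would fire is therefore uncertain, especially under the either-condition wording. That the paired t test concerns the differences, and that McNemar's test answers another question, rests on none of these assumptions.

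**What to change.** Replace the whole sentence in Data Analysis, including the choice between the two tests. Deleting only the opening clause would leave two tests and no rule for choosing between them. Suggested text:

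*Change in PHQ-9, GAD-7 and knowledge/skills scores will be analysed by the mean within-person difference with its 95% CI and paired t test, whatever the distribution of the raw scores. The distribution of the differences is examined only as a diagnostic, with a bootstrap CI (or signed-rank test) as a sensitivity analysis. McNemar's test is used only for binary outcomes.*

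Results states that data were collected in 2022-2023 and that analysis was ongoing in April 2024, so the change should be declared as made after data collection. The required sample size stays at 112 and no new data are needed. The cost is one replaced passage and one extra sensitivity analysis.

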### Phase 2: Intervention Rollout

#### Eligibility Criteria for Participant Enrollment in Intervention

Residents who are 18 years of age and older, who are SP for “mild” or “moderate” symptoms of anxiety or depression as determined by the GAD-7 and PHQ-9, are recruited for the mPareshan intervention. Individuals receiving therapy or pharmacological treatment for mental health issues and exhibiting severe anxiety or depression with danger signs (self-harm, harm to others, and suicidal ideation) are not included in the study.

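### McNemar's test is named as the distribution-dependent alternative to the paired t test for numeric scores, but it needs a binary outcome that the plan does not define

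*Protocol article*

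**What the plan says.** In the protocol article, Data Analysis, the rule opens "Depending on the distribution of anxiety or depression scores of SPs and knowledge or skills scores of health workers" and then states that paired t tests or "McNemar’s chi-square tests will be used to evaluate the change in outcomes". The next sentence adds: "The mean difference with 95% CIs will be reported". No rank-based paired test is named.

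The outcomes under this rule are numeric. For the PHQ-9, the HH Survey section says "The maximum possible score is 27 and the minimum score is 0"; the GAD-7 runs from 0 to 21. Aims and Objectives and End Line Quantitative Assessment both frame the clinical outcome as change in mean score. Severity bands exist for both scales ("Scores 5, 10, 15, and 20 represent cutoff points for mild, moderate, moderately severe, and severe depression, respectively"; "Scores of 5, 10, and 15 are taken as the cutoff points for mild, moderate, and severe anxiety, respectively"), but none is tied to a binary outcome for change.

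Under Eligibility Criteria, residents with mild or moderate anxiety or depression "are recruited for the mPareshan intervention". Study Procedure Outline also joins the two conditions with 'or', whereas HH Survey joins them with 'and'.

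**The concern.** The usual alternative to a paired t test for non-normal differences is a rank-based test or a resampling interval. McNemar's test is neither. To run it, the analyst must first dichotomise each score, and the plan does not say where. That replaces a question about mean change with one about a proportion crossing a line, so the P value and the promised mean difference would no longer describe the same quantity.

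For SPs there is a further hazard. They are enrolled because they score at or above a threshold. If that same threshold defines the binary outcome, movement can be counted in one direction only, and the symmetry that McNemar tests is broken by selection before any counselling takes place.

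**Working it through.** **1. What the trial was sized for.** Sample Size Calculations gives a mean difference of 1.5, SD 5.6, 5% significance, 80% power and a minimum of 112. With two-sided alpha assumed, the normal approximation for a paired mean is n = (5.6 × (1.960 + 0.842) / 1.5)² = 109.4, so 110. With the noncentral t distribution, power is 0.799 at n = 111 and 0.802 at n = 112. The stated 112 is reproduced exactly as a paired t test, so the design targets a paired mean and not a paired proportion.

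**2. McNemar with an empty cell.** Let b be the number going from positive to negative and c the number going from negative to positive. If every analysed SP is positive at baseline on the chosen split, c = 0.

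- Exact two-sided: P = 2 × 0.5^b. b = 5 gives .0625; b = 6 gives .031.
- Uncorrected chi-square: (b − c)²/(b + c) = b. It passes 3.84 at b = 4 (P = .0455).
- Continuity-corrected: (b − 1)²/b. b = 5 gives 3.20; b = 6 gives 4.17 (P = .041).

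The Results section reports 98 SPs. Assuming all have an end line score, significance needs 4 to 6 of them (4% to 6%) to fall below the cut for any reason. The binomial probability of 6 or more is 0.37 if the true share falling below is 5%, 0.81 at 8%, 0.94 at 10% and 1.00 (rounded) at 15%.

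**3. Rejection with no true change, n = 98.** The documents give no score distribution or retest correlation, so these are assumptions: geometric (right-skewed) scores, 30% or 50% of the population at 5 or more (30% echoes the prevalence assumed for the baseline survey), retest correlation 0.5 to 0.95 for one scale and 0.5 to 0.9 for two, correlation between PHQ-9 and GAD-7 0.5 to 0.7, selection of scores up to 14, continuity-corrected McNemar.

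| Selection and binary split | Negative at baseline | McNemar rejects |
|---|---|---|
| One scale selects; same scale split at 5 | none | 0.99-1.00 |
| Either scale selects; split on either scale at 5 or more | none | about 1.00 |
| Either scale selects; PHQ-9 split at 5 | 27-35% | 0.30-0.83 |
| PHQ-9 split at 10 | some | about 0.02-0.11 |

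In the one-scale runs, 13% to 50% of SPs fall below 5 at retest through measurement noise alone.

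**4. The paired t test in the same runs.** It rejects in 0.05-0.28 of trials when either scale selects and in 0.05-0.97 when one scale selects, because of regression to the mean. What is specific to McNemar shows where the two tests part. With 50% at 5 or more and retest correlation 0.84 or higher on one scale, the t test stays at about 0.05 while McNemar at a cut of 5 still rejects in at least 0.99.

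**5. Health workers.** The 72 health workers are not selected on a score. The mismatch between test and data applies to them; the empty cell does not.

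**The case against.** The strongest reply is that the main analysis is clear from the rest of the article. The outcome is change in mean score, the sample size is a paired mean, and the mean difference with CI is promised whichever test is used. On that view McNemar is a loosely worded reference to categorised outcomes, and any cutoff may sit in an analysis plan that is not shown. This stands in part. The missing cutoff is not in itself a fault of a condensed article, and the mean difference would probably still be reported. But the sentence makes the distribution of scores the deciding factor, not the type of variable, and that rule is wrong as written.

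It is also fair that nothing shows the fallback would be triggered. The paired t test depends on the distribution of the differences, and selection removes the upper tail at baseline.

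A reader might infer that McNemar would reject almost automatically in this trial. The documents do not support that. It requires a split at the selection threshold of the selecting scale, or on SP status itself, and no split is named. HH Survey gives sensitivity and specificity at a cut of 10, where the simulated rate is about 0.02-0.11. With either scale qualifying a person, some SPs are negative on PHQ-9 at baseline and changes run both ways. The wording in HH Survey that requires both conditions would restore the empty cell at a cut of 5 on each scale, but the sections disagree on this.

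**Conclusion.** The rule is wrong as stated, for SPs and health workers alike. McNemar's test is not an alternative to the paired t test for non-normal scores, no binary outcome is defined for it, and it cannot deliver the promised estimate. This part rests on the text alone.

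The inflated false-positive rate is conditional. It is about 99-100% if SPs are split at their selection threshold, about 0.30-0.83 for PHQ-9 of 5 or more under the either-scale rule, and near or modestly above nominal at a cut of 10. The counts of 4 to 6 conversions follow from arithmetic; the rejection rates depend on the assumed score shape and correlations. The spread is itself a reason to settle the rule, because the error rate turns on a choice that the article leaves open.

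A reader might also infer that dropping McNemar makes a significant change attributable to the counselling. It does not. Regression to the mean in a selected single-arm cohort also affects the paired t test.

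**What to change.** Replace the test-selection sentence with wording such as: *Change in PHQ-9, GAD-7, knowledge and skills scores will be estimated as the mean paired difference with 95% CI (paired t). If the paired differences are clearly non-normal, a bootstrap 95% CI for the same mean difference will be used, with the Wilcoxon signed-rank test as a sensitivity analysis.*

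Restrict McNemar's test to a binary outcome whose cutoff is fixed beforehand. Do not test SP status at the selection cutoff; report the proportion below it at end line descriptively with a CI. State alongside the results that regression to the mean may account for part of any pre-post change.

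The cost is a short rewrite of the analysis paragraph and no new data. The article describes analysis as ongoing, so the change should be made, and recorded with its date, before results are reported.
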